## Abstract

**Background:**

Type 1 diabetes is a disease with complex therapeutic recommendations that require day-to-day lifestyle changes. Motivational Interviewing is a communication tool that has proved effective in changing behaviors in people with addictions, obesity and type 2 diabetes. Our objective is to evaluate the effects of a Motivational Interviewing intervention in people with type 1 diabetes.

**Methods:**

Sixty-six patients with type 1 diabetes and hemoglobin A1c >= 8% have been included and randomly assigned (computer-generated sequence, sealed envelopes, ratio 1:1) either to the intervention or to the control group. In the intervention group, appointments every 4 months with the endocrinologist include Motivational Interviewing; in the control group, the appointments proceed as usual. Patients will be followed for 16 months. The primary outcome will be self-care behaviors, assessed by a validated questionnaire, the Diabetes Self-Care Inventory-Revised Version. Secondary outcomes include: HbA1c, motivation for self-care, self-efficacy, health-related quality of life, satisfaction with professional-patient relationship, and fulfillment of patients’ own objectives. The practitioners receive training in Motivational Interviewing in order to help them promote adherence to self-care, encourage patient motivation and improve the doctor-patient relationship. The Motivational Interviewing intervention will be evaluated by two psychologists, blinded to the assigned treatment, through video recordings of the sessions and the administration of a purpose-built questionnaire, the EVEM 2.0 scale.

**Discussion:**

There is evidence that MI can improve self-care in type 2 diabetes. In this study, we aim to evaluate the effect of MI on self-care and HbA1c in people with type 1 diabetes.

**Clinical Trial Registration:**

https://clinicaltrials.gov/ct2/show/NCT03906786, identifier NCT03906786.

## Highlights

Research has shown that the level of motivation reported by the patient was the strongest predictor of adherence to self-care, and was also recognized as one of the greatest obstacles to adherence to treatment.Motivational Interviewing has shown to be effective in changing behaviors in people with addictions, obesity, and type 2 diabetes.The present trial will assess the effects of Motivational Interviewing on adults with type 1 diabetes.

## Background

People with type 1 diabetes (T1D) have to carry out a series of complex tasks every day in order to manage their disease and maintain good glycemic control (1). These tasks include glucose measurements, multiple insulin injections, carbohydrate counts in the diet, and management of hypoglycemia and hyperglycemia. In addition, patients must continuously make decisions regarding the adjustment of their insulin treatment and the everyday problems related to their illness (2–4). In a previous study which identified multiple factors related to self-care, the level of motivation reported by the patient was the strongest predictor of adherence to self-care, and was also recognized as one of the greatest obstacles to adherence to treatment (5). Currently, diabetes management is focused on person-centered care and empowerment, a philosophy that encourages patient involvement, awareness and participation in decisions concerning their health (6). One of the fundamental pillars for promoting empowerment of people in their self-care is therapeutic patient education (7, 8). Therapeutic patient education provides patients with the knowledge, tools and skills needed to facilitate informed decision-making and self-management of the disease (8). However, therapeutic education alone does not guarantee the involvement of patients in the care of their health (8, 9).

Since 2014, in its *Standards* for *Diabetes* Self-Management *Education and Support*, the American Diabetes Association recommends a set of evidence-based communication strategies which have been shown to facilitate behavioral changes and to complement therapeutic patient education. They include cognitive strategies, problem solving, enhanced self-efficacy, relapse prevention strategies and Motivational Interviewing (MI) (10, 11). To quote the creators of MI: “Motivational Interviewing is a collaborative, goal-oriented method of communication with particular attention to the language of change. It is designed to strengthen an individual’s motivation for and movement toward a specific goal by eliciting and exploring the person’s own argument for change within an atmosphere of acceptance and compassion” (12).

MI emerged for the first time in Norway in 1982, and initially focused on addictions (13). Since then, its use has spread to other areas. It has been widely applied in the management of behavior-associated diseases (14) and more than three decades of research have established it as an effective approach for improving a series of health-related behaviors (14). Currently, there is moderate, consistent and robust evidence that MI achieves behavioral changes and improves adherence to treatment in patients with alcohol abuse, unhealthy lifestyles (e.g., sedentarism, overeating) and obesity/overweight (15, 16). Brief 15-min MI interventions have also proven to be effective, though the probability of success increases with the number of encounters and with longer follow-up periods (14).

MI has been shown to be effective in improving glycemic control in people with type 2 diabetes (T2D) (16–20) and its superiority over cognitive behavioral therapy has also been demonstrated (21). MI has proved effective in reducing HbA1c in adolescents with T1D (22, 23), and in a clinical trial it also improved quality of life (24, 25). It is effective as a complement to therapeutic education (26) and to other treatments, or as an independent treatment (22). However, not all studies have reported improvement in glycemic control in T1D or T2D (27, 28). A recent systematic review, which included four randomized controlled trials, concluded that there is some evidence of benefit of MI in people with T1D, but that more research is needed to isolate the effect of MI alone on adherence to treatment and HbA1c (29).

### Objective and Hypothesis

The purpose of this randomized controlled clinical trial is to study the impact of the application of MI in routine follow-up visits of patients with T1D and poor metabolic control.

The hypothesis is that an intervention with MI can increase patients’ self-care behaviors, reduce HbA1c, enhance their self-efficacy and health-related quality of life, and improve the doctor-patient relationship.

## Methods

This study protocol was developed in accordance with the Recommendations for Interventional Trials 2013 Statement (SPIRIT 2013) and the Consolidated Standards of Reporting Trials statement (CONSORT 2010) when applicable.

### Theoretical Framework

MI is defined primarily by its spirit: that is, a style that nurtures the interpersonal relationship between the therapist and the patient. It explains how the process of change is formed by different stages and how people are more likely to abandon a habit at certain stages than at others. In addition, it considers that deciding to change, to commit oneself, and to take responsibility for a therapeutic process is key to achieving behavior changes. MI uses a style of collaborative communication focused on one or several objectives and pays special attention to the language of change. It is designed to strengthen personal motivation and commitment to a specific goal, eliciting, and exploring the reasons that the person has for changing, in an atmosphere of acceptance and empathy. The approach is based on patient-centered counseling, cognitive therapy, systems theory and the social psychology of persuasion. It integrates clinical skills that promote motivation, combining managerial and non-managerial elements. In sum, it is a practical and specific contribution to daily life in which language is used to influence behavior by helping individuals express their own internal motivations, and guiding conversations in such a way that people persuade themselves to change in accordance with their own values and interests.

For maximum benefit to be derived from MI, the interviewer must have received adequate training, but must also believe in it in order to be able to influence the patient and initiate a process of change. MI involves eliciting from the patient what they already know and have, rather than giving them what they lack (for instance, knowledge, or medication) (30). This focus can improve patients’ motivation, since they choose what they want to do or change, not what others want them to do or change. By developing MI skills, practitioners can help patients identify what matters to them and then use these motivations to bring about changes in their health behavior (30).

Assessing the effectiveness of MI in the context of diabetes may appear controversial, since adherence to self-care already obliges people with diabetes to carry out multiple tasks. In fact, previous studies have focused on assessing the impact of MI on glycemic control (14, 17); to date, there are no clinical trials that study its impact on adherence to self-care behaviors in adults with T1D, or evaluate the standardized application of MI by practitioners.

### Study Design and Setting

This randomized, controlled, single-blind, parallel group clinical trial is carried out at the Endocrinology and Nutrition service of the Insular University Hospital, Las Palmas de Gran Canaria, a reference center in its area for the care of people with T1D.

### Participants and Recruitment

A total of 66 people with T1D have been included in the study and will be followed over a period of 16 months. Patients who met the inclusion criteria were informed of the nature of the study and invited to participate. Subsequently, they were recruited by their endocrinologist at the outpatient clinics of the Endocrinology and Nutrition Service of the Insular University Hospital. The recruitment period lasted from March to August 2019.

### Inclusion Criteria

Diagnosis of T1D, age over 18, at least one year of disease duration, HbA1c >= 8% and/or severe hypoglycemia in the previous 6 months.

### Exclusion Criteria

Pregnancy either in progress or scheduled in the following 12 months; any other circumstance that, in the opinion of the investigators, might interfere with the follow-up.

Patients who meet the inclusion criteria receive written information regarding the study and are invited to participate. They are also provided with more information by phone, when they are reminded that the trial will begin at the next scheduled follow-up appointment. At this first appointment, prior to the consultation, the participants sign the informed consent document and fill in a dossier that records all the clinical, sociodemographic and psychosocial variables. These variables are listed in the Measures section below.

### Randomization and Blinding

The participants are randomly assigned to the intervention group or control group. A computer-generated randomization list (with a 1:1 ratio) is used for each endocrinologist to prepare the labels indicating the assignment of each patient, which is kept in sealed envelopes, numbered consecutively, and stored at the unit. At the time of inclusion of a patient in the study (appointment 1), the appropriate envelope is chosen and opened to show the endocrinologist the treatment assigned. The randomization is stratified by practitioner and the treatment assigned to the first participant each day is applied to all participants scheduled on that day, in order to facilitate the application of the MI and avoid contamination between treatment groups. To limit possible bias, patients are not informed of the assigned treatment. The informed consent document explains that the study will evaluate the effects of the doctor-patient communication, though without going into detail. The researcher who generated the randomization list and prepared the envelopes for the assignment of the treatment group will not be involved in the treatment or evaluation of the participants; likewise, the researchers who will rate MI compliance and analyze the data will be blind to the treatment allocation.

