### Analysis

Based on the number of patients followed in the clinic and the percentage with an HbA1c above 8%, we estimated that each of the three clinical researchers involved in the trial would be able to recruit around 20 patients in 4 months. With an expected sample size of 60 participants, we would be able to detect inter-group differences of 12.8 points on the SCI-R questionnaire and of 0.85% in HbA1c, with a power of 90% and a two-sided alpha of.05 [assuming an SD of 15 points in the SCI -R and 1% in HbA1c in line with previous studies (5)]. The equivalent detectable differences with a power of 0.8 would be 11 points and 0.74% respectively (calculated with http://hedwig.mgh.harvard.edu/sample_size/js/js_parallel_quant.html). This was an approximate estimation assuming the normality of the variable.

In order to retain most of the patients during follow-up, if someone misses an appointment, the patient is contacted and the visit is re-scheduled. Specific efforts will be made for the final evaluation visit. If a physical appointment cannot be achieved, the questionnaires will be sent and completed by e-mail or, if this is not feasible, the patient with be interviewed by phone. We expect the loss to follow-up to be below 10%.

Intention to treat analysis will be performed: i.e., all randomized participants who have attended at least one intervention (or control) session will be included in the analyses. The main analysis for primary and secondary outcomes, except HbA1c, will be a generalized linear model (GLM) including the intervention arm, the baseline score of the dependent variable and other variables imbalanced at baseline as covariates. The dependent variable will be the post-intervention score. The GLM does not need a normal distribution in the dependent variable (38), although the distribution of the variables will be analyzed using de Shapiro- Wilk test to perform an adequate descriptive analysis. The choice of the link function will depend on the distribution of the variable.

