For the HbA1c, a GLM for multilevel analysis will be used including the intervention arm, baseline HbA1c and other imbalanced variables in the baseline as covariates. First-level are those corresponding to each measurement along follow-up (repeated time measurements); the second level includes patients’ variables. The model will also include an interaction term between the intervention-arm and time (follow-up), allowing for differences in the intervention effect between follow-up assessments (39). The effect that identifies the intervention arm is considered fixed, whereas the intercept is considered random. An autoregressive [AR (1)] covariance structure will be used in the model.

Other variables will be added as confounders in the model, as secondary sensitivity analyses. We will first fit separate models including each confounder, one at a time. Those variables whose inclusion in the model changes the estimates’ treatment effect by at least 10% will be considered as confounders. As suggested in the CONSORT statement, decisions about confounders will not be based on P value  (40).

In the case of missing values, these will be accommodated with multiple imputation procedure in Stata 15.0 software (Stata Corporation) (41). This procedure saves cases for the analysis and can be considered an intention-to-treat analysis. Analysis under multiple imputations is valid for randomly missed data (42). A threshold of.05 will be used to define the statistical significance of those tests.

For the MIAS/EVEM 2.0 scale, the Intraclass Correlation Coefficient (ICC) will be used.

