We acknowledge that this study has some limitations. MI is a complex tool to learn; it takes time to manage it correctly, practitioners may not be experts in its use and learned skills tend to wear off. In order to reduce training erosion, regular coaching and feedback will be provided throughout the trial. On the other hand, the same practitioner will apply MI to some patients and the traditional interview to the others (control group), which carries a certain risk of contamination between the study groups. To minimize contamination, participants seen by the same practitioner on the same day were assigned to the same treatment group, which could, of course, lead to some imbalance between the sizes of the groups. To monitor if MI is indeed applied in the intervention group and not in the control group, the sessions will be blindly evaluated at the first and last visits of the study. Finally, not all patients are comfortable with this method of interviewing, a situation that may hinder its application. Regarding outcomes, self-care, the primary outcome, comprises an array of behaviors, which might not accurately reflect the success of MI if change is focused on a single behavior, selected by the patient. The assessment of the achievement of self-defined goals should, at least partially, account for this drawback. Furthermore, some concepts will be examined on an exploratory basis using only a single-item and not a psychometrically tested measure, so these findings should be interpreted as descriptive and with caution. Finally, the sample size of this trial will be able to detect relatively large, clinically relevant changes in the primary and some of the secondary endpoints. However, it might be underpowered to detect smaller, albeit still relevant effect sizes. The low number of healthcare professionals included in the trial, which act as randomization clusters, does not allow the effect associated with the health professionals to be included in the analysis. This could potentially lead to bias, since the variance associated with the healthcare professionals cannot be estimated.

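### Treatment is allocated by practitioner-day, but the models and stated detectable differences treat patients as independent, so standard errors may be too small by an amount the protocol does not let us determine

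*Protocol article*

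**What the plan says.** **Allocation.** Under Randomization and Blinding, "A computer-generated randomization list (with a 1:1 ratio) is used for each endocrinologist", and "The randomization is stratified by practitioner". The same section adds that "the treatment assigned to the first participant each day is applied to all participants scheduled on that day". The Discussion confirms that "participants seen by the same practitioner on the same day were assigned to the same treatment group", which makes the unit one practitioner on one day.

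**Analysis.** The primary model is a GLM for the post-intervention score, with arm, baseline score and covariates imbalanced at baseline. The HbA1c model has two levels: "First-level are those corresponding to each measurement along follow-up (repeated time measurements"), with patients as the second level. It has a random intercept and an AR(1) structure. Neither model mentions the day of allocation or the practitioner.

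**Sample size.** "With an expected sample size of 60 participants, we would be able to detect inter-group differences of 12.8 points on the SCI-R questionnaire", at 90% power and two-sided alpha 0.05, assuming an SD of 15. The companion figures are 0.85% for HbA1c (SD 1%) and, at 80% power, 11 points and 0.74%.

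**Limitations.** The Discussion gives possible group-size imbalance as the consequence of same-day allocation. It then describes the professionals as the randomization clusters and says that they are too few for their effect to be included in the analysis.

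**The concern.** A second or third participant on a practitioner's day has no random draw of their own. If outcomes of same-day participants are positively correlated, the difference between arms varies more than a model with independent patients assumes. Intervals are then too narrow, the nominal 5% test rejects too often under the null, and the design detects less than stated.

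Some correlation is plausible. Same-day participants share the practitioner's stage of skill in Motivational Interviewing, and the protocol itself says that this skill takes time to acquire and tends to wear off.

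The limitations paragraph does not cover the problem, because it names a different unit. Each professional has a separate 1:1 list and treats both arms, so professionals are strata. Its reason for leaving clustering out, too few units, applies to three professionals but not to the practitioner-days. At an average of 1.5 to 3 participants per day (assumed), 66 patients form 66/1.5 = 44 to 66/3 = 22 such days.

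**Working it through.** **Inputs from the protocol article.** 60 participants expected (30 per arm), 66 recruited; SD 15 points (SCI-R) and 1% (HbA1c); two-sided alpha 0.05; three endocrinologists; recruitment March to August 2019.

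**Inputs not given, so assumed.** Participants per practitioner-day, m, and the within-day ICC. When day sizes vary, the m that matters is the size-weighted mean, Σm²/Σm.

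**Step 1: reproduce the stated figures.** For two independent means with 30 per arm, the noncentral t (58 df) gives:
- SCI-R: 12.77 points at 90% power and 11.03 at 80% (stated 12.8 and 11).
- HbA1c: 0.851% and 0.736% (stated 0.85% and 0.74%).

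All four match with a design effect of exactly 1.

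**Step 2: add the design effect.** DE = 1 + (m − 1) × ICC. The detectable difference is multiplied by √DE. A nominal 5% test that ignores clustering has actual alpha 2 × [1 − Φ(1.96/√DE)].

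| m | ICC | DE | True SE / planned SE | Actual alpha | SCI-R difference, 90% power |
|---|---|---|---|---|---|
| 1 | any | 1.000 | 1.000 | 5.0% | 12.8 |
| 1.5 | 0.01 | 1.005 | 1.002 | 5.1% | 12.8 |
| 1.5 | 0.05 | 1.025 | 1.012 | 5.3% | 12.9 |
| 2 | 0.05 | 1.050 | 1.025 | 5.6% | 13.1 |
| 2 | 0.10 | 1.100 | 1.049 | 6.2% | 13.4 |
| 3 | 0.05 | 1.100 | 1.049 | 6.2% | 13.4 |
| 3 | 0.10 | 1.200 | 1.095 | 7.4% | 14.0 |

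For m = 3 and ICC 0.10: DE = 1 + 2 × 0.10 = 1.20, √1.20 = 1.095 and 12.77 × 1.095 = 13.99. Power at 12.8 points (normal approximation) falls from 0.911 to 0.855. The HbA1c difference, computed as in the protocol from a single two-sample comparison, rises from 0.85% to 0.93%.

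**Step 3: check by simulation.** The baseline-adjusted linear model was fitted ignoring clusters, in 5,000 runs. Type I error was 5.5% (m = 2, ICC 0.05) and 7.3% (m = 3, ICC 0.10), against 5.6% and 7.4% from the formula.

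**Step 4: which m is plausible?** 66/3 = 22 patients per practitioner over about 26 weeks is 22/26 = 0.85 per week. Assume one clinic day a week and Poisson arrivals. The mean size of a non-empty day is then 0.85/(1 − e^−0.85) = 1.5, and the size-weighted mean is 1 + 0.85 = 1.85. At m = 1.85 and ICC 0.05, DE is 1.04, alpha about 5.5% and the difference 13.0 points. At ICC 0.10 these are 1.08, 6.0% and 13.3. More clinic days per week would lower m, and fewer would raise it.

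**The case against.** The strongest reply is that the effect may be very small, and several parts of it stand.

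- **Small clusters.** The recruitment rate suggests few participants per practitioner-day (Step 4).
- **Low correlation.** Each patient has an individual visit of 15 to 20 minutes, and the SCI-R is measured at 16 months. A shared first appointment date is a weak source of correlation that much later. A practitioner's skill also carries over to neighbouring days, so clustering on day would capture it only in part.
- **Offsetting errors.** Leaving out practitioner, the stratification factor, usually makes standard errors too large. The stated detectable differences also ignore the gain from baseline adjustment: with a baseline correlation of 0.5 (assumed), variance falls by 25%, which offsets a DE of up to 1/0.75 = 1.33. That gain concerns the detectable difference only and does not correct the type I error.
- **Partial candour.** The protocol calls its calculation approximate and concedes that the trial may be underpowered for smaller effects.

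A reader might infer that the standard errors and p-values are certainly too small. The documents do not support this: it needs both shared days and a positive ICC, and neither is reported. A reader might also fear a type I error near 12% or a detectable difference near 16 points. Those values need m = 4 together with ICC 0.20, a corner case that nothing in the protocol supports.

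What the reply does not remove is the mismatch itself. Nor is this a detail left to an analysis plan. The article fixes the covariates, the levels, the random effect and the covariance structure, and it identifies the cluster wrongly.

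**Conclusion.** The point holds in conditional form. Allocation is by practitioner-day, the stated models and detectable differences assume independent patients, and the limitations paragraph names strata as clusters.

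Standard errors and p-values may therefore be too small, and the detectable differences optimistic. For the assumed range of 1.5 to 3 participants per day and ICC 0.01 to 0.10, standard errors are understated by about 0.2% to 10%, with the type I error and SCI-R differences shown in the table. Larger clusters, unequal cluster sizes or a higher ICC would make it worse. An ICC near zero, or nearly all days with a single participant, would make it negligible. The practitioner stratum and baseline adjustment may offset part of it.

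This should be fixed, because the actual cluster sizes are knowable and the protocol's own reason for not modelling clusters does not apply to the true unit. It does not invalidate the trial.

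**What to change.** 1. Derive a practitioner-day identifier from the practitioner and the date of appointment 1, when the envelope is opened.
2. In the primary, secondary and HbA1c models, use standard errors clustered on practitioner-day with a small-sample correction. Use a practitioner-day random intercept only if it is estimable; with many single-patient days it may not be.
3. Include practitioner as a fixed effect. Three levels cost two parameters, and no between-practitioner variance has to be estimated.
4. Report the number of practitioner-days per arm and the distribution of their sizes.
5. Restate the detectable differences with DE = 1 + (m − 1) × ICC, with m as the size-weighted mean, over a range of ICC.
6. Correct the limitations paragraph: practitioner-days are the clusters, and practitioners are strata that each treat both arms.

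The cost is one derived variable and revised analysis wording. Intervals may be slightly wider and the stated detectable differences slightly less favourable. No new patients are needed. Recruitment is complete, so the restated figures serve interpretation and change no design decision.
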